## Abstract

**Introduction:**

Parenting interventions have shown promise in improving mental well-being for parents and children and strengthening family relationships. Parenting for lifelong health (PLH) is an open-access, evidence-informed programme that aims to improve positive parenting practices, reduce family violence and promote mental health, particularly in low-resource settings. This study will evaluate the implementation and (cost-)effectiveness of an adapted version of the PLH for Parents and Teens programme. It will focus on supporting positive parenting, communication, mental health and well-being of adolescents and their caregivers in North Macedonia and Moldova.

**Methods and analysis:**

This multicountry hybrid type 1 effectiveness-implementation randomised waitlist-controlled trial will recruit 660 adolescents aged 10–14 years and their caregivers through schools, Youth Clinics and community partner organisations, including vulnerable and linguistically diverse families. The intervention group will receive the adapted PLH programme with assessments conducted postintervention and at 6-month follow-up. The waitlist control group will receive the adapted PLH programme after completion of the intervention group’s 6-month post-baseline assessment. Primary outcomes include adolescent emotional problems, family functioning, parenting practices, adolescent and caregiver quality of life. Secondary outcomes assess a range of mental well-being, family and other psychosocial outcomes. Other prespecified outcomes include implementation and cost outcomes. Primary analyses will compare intervention and waitlist control groups at postintervention and 6-month follow-up using intention-to-treat, baseline-adjusted linear mixed models. A within-trial economic evaluation will include cost–utility analysis and cost-effectiveness analysis. A macroeconomic analysis will assess broader economic impacts using public financing and budget impact analysis. The study uses a mixed-methods process evaluation, and integrates qualitative data, budget impact analysis and simulation modelling to inform scale-up considerations.

**Ethics and dissemination:**

The study has received ethical approval from all relevant sites. Results will be disseminated through peer-reviewed publications, scientific conferences and webinars, newsletters, social media and open-access platforms, alongside engagement with researchers, clinicians, policymakers and the public. The Family-Focused Adolescent & Lifelong Health Promotion project uses a targeted communication and dissemination strategy for families, implementers and policy stakeholders to promote the adoption and scale-up of evidence-informed, open-access parenting interventions for adolescents and caregivers in low-resource settings. Dissemination focuses primarily on North Macedonia and Moldova while also engaging actors across the wider Eastern European region.

**Trial registration number:**

NCT07240571.

STRENGTHS AND LIMITATIONS OF THIS STUDYThis study uses the Multiphase Optimisation Strategy framework to systematically develop, refine and optimise the intervention through sequential preparation and factorial testing, integrating findings across all three phases (preparation, optimisation and evaluation) to strengthen confidence in the final intervention package.This study uses a type 1 hybrid effectiveness-implementation design with robust process evaluation and integrated economic evaluation to assess intervention effects, implementation, cost-effectiveness and scalability.This study uses targeted recruitment strategies to increase participation of linguistically diverse and socially vulnerable families, improving equity and inclusion.This study uses a 6-month follow-up period, which limits conclusions about the long-term sustainability of intervention effects.This study recruits families mainly through schools and service networks, which may limit generalisability to less service-connected populations.

## Introduction

 Adolescence is a transitional phase between childhood and adulthood and represents a critical period for the onset of mental health conditions and the formation of foundational health behaviours.^1
2^ Anxiety and depressive disorders are among the most common mental health conditions in youth.^3^ Positive relationships with family and peers can support adolescent health, whereas experiences such as bullying, social exclusion and conflict can contribute to emotional distress and mental health problems.^4^ Parental mental health and parenting styles can also have significant effects on adolescent health.^5^ Children exposed to family violence are at increased risk for a range of mental and physical health problems, and interparental conflict is associated with social anxiety and loneliness.^6^ In contrast, positive parenting practices and good communication are linked to better health outcomes.^7–9^ During adolescence, family relationships become particularly vulnerable, highlighting the importance of interventions that promote supportive parenting and reduce harsh parenting practices.^10^

Adolescents are also affected by broader social and environmental stressors. Poverty, housing instability and academic pressure can lead to chronic stress and mental health challenges.^11^ In Eastern Europe, youth face additional risks related to economic insecurity, post-COVID impacts, interpersonal violence and the ongoing war in Ukraine.^12^ In the Republic of North Macedonia and the Republic of Moldova, family separation due to migration or work abroad, as well as limited access to youth friendly mental health services, further increase vulnerability.^13
14^ The WHO recommends integrating mental health support into broader health strategies, including training for primary caregivers.^15^ Working with adolescents and caregivers on supportive relationships and good communication may help partly buffer the impacts of some of the wider risk factors.^16^

Programmes focusing on family relationships and parenting skills have emerged to be a promising strategy to enhance well-being and prevent mental health risks in children and young people.^17^ Such programmes aim to impart knowledge, embed skills and provide support to strengthen the caregiver and child relationships.^18^ Recent evaluation shows that early parenting interventions are effective in preventing child mental health problems across diverse cultures, clinical and socioeconomic settings.^19^ While originally programmes focused only on parents, increasingly they also involve older children and adolescents as active participants.

Parenting for lifelong health (PLH) is one such evidence-informed intervention, developed through collaboration among academic researchers, the WHO and UNICEF to support families in low- and middle-income countries.^20–23^ Randomised controlled trial (RCT) evidence showed that participation in the PLH for Young Children programme involving caregivers of children aged 2–9 years has been associated with significant improvements in positive parenting practices (Foran *et al*, forthcoming) and short-term reductions in child externalising behaviours, compared with an active control condition (Heinrichs *et al*, forthcoming) in Moldova, North Macedonia and Romania.

Although parenting interventions have shown promise in improving child and caregiver mental well-being, evidence on their impact on adolescent mental health remains limited.^24
25^ The current study will address this gap by evaluating the PLH for Parents and Teens programme, adapted with a specific focus on adolescent mental health, and using a range of relevant outcome measures. In addition, while interest in scaling up parenting programmes is growing, many studies focus primarily on effectiveness and pay less attention to implementation and scalability.^26
27^ To address this limitation, the study will include a process evaluation and consultations with stakeholders and families, including adolescents and caregivers, to inform programme adaptation and better understand opportunities for scale-up.

This study represents the final phase of the Family-Focused Adolescent & Lifelong Health Promotion (FLOURISH) project, which aims to (1) adapt, (2) optimise and (3) evaluate the implementation and (cost-)effectiveness of a PLH-based intervention targeting adolescents aged 10–14 and their caregivers in North Macedonia and Moldova (see Attachment 3 for more details on the other project phases). In this protocol, we describe plans for an RCT focusing on implementation, (cost)-effectiveness and scalability to address the following research questions:

How is the adapted PLH programme implemented by the intervention staff and how do the adolescents and caregivers participate in it? What is the variation in implementation and attendance?What is the effectiveness of the adapted PLH programme on the primary outcomes postintervention and at 6-month follow-up?What is the effectiveness of the adapted PLH programme on secondary outcomes postintervention and at 6-month follow-up?What are the costs, quality of life outcomes and cost-effectiveness of the adapted PLH programme?How do the stakeholders perceive the prospects for scaling-up the programme?What are the required resources for scaling up the programme at national level and what is their budget impact?

This RCT will test the following hypotheses:

Adolescents and caregivers in the intervention group will show more favourable average scores on primary and secondary outcomes in the adapted PLH for Parents and Teens programme compared with the waitlist control group at post-intervention and at 6-month follow-up.The adapted PLH programme will be more cost-effective compared with the waitlist control group, as measured by incremental cost per quality-adjusted life-year (QALY) and capability-weighted life year (CWLY) gained.The adapted PLH programme will be implemented with high fidelity and participant attendance, with feedback from participants and staff indicating high satisfaction and positive perceived impacts.Stakeholders will be supportive of programme scale-up and identify a range of opportunities and challenges related to the long-term funding of the programme.

## Methods

### Study design

The FLOURISH project is guided by the Multiphase Optimisation Strategy framework, implemented across three interrelated phases^28
29^: phase 1 (preparation),^30^ phase 2 (optimisation)^31^ and phase 3 (evaluation). This study (phase 3) uses a multicountry parallel-group RCT design with assessments at baseline, postintervention and 6-month follow-up to evaluate the adapted PLH programme for adolescents aged 10–14 years and their caregivers in North Macedonia and Moldova. This hybrid type 1 effectiveness-implementation trial examines implementation, (cost)-effectiveness and scalability.^32^ The intervention group will receive the adapted PLH programme immediately, while the waitlist control group will receive the programme after the intervention group’s 6-month follow-up.

The waitlist control design was selected to ensure that all participating families are eventually offered access to the intervention given the limited availability of comparable services in the participating settings. This approach was co-designed by researchers and implementers and was considered important for participant recruitment and retention. As part of the enrolment procedures, participants complete an exclusionary statement regarding acute distress and severe mental or physical health conditions that may interfere with participation. Individuals who self-identify as unable to participate due to health reasons are contacted by the research team and provided with information about appropriate support services. Enrolled participants are permitted to access usual care and other community-based support services during the trial. Participation in additional parenting programmes, counselling or mental health services will be recorded at each assessment to account for their potential influence on study outcomes.

To understand programme implementation and scalability, the trial includes an embedded mixed-methods process evaluation and public consultations. This approach aims to facilitate the adoption and dissemination of open-source, evidence-based family interventions for adolescents in low-resource settings.

The study was preregistered on ClinicalTrials.gov (NCT07240571; see Note), received ethical approval and will be reported in accordance with the Consolidated Standards of Reporting Trials (CONSORT) guidelines.^33^ The Standard Protocol Items: Recommendations for Interventional Trials (SPIRIT) Checklist for the protocol is also included as online supplemental appendix 1.^34^

### Study setting

Intervention implementation is conducted in two Eastern European countries, North Macedonia and Moldova, and is supported by two established health networks with prior experience delivering PLH programmes. In North Macedonia, the Institute for Marriage, Family and Systemic Practice (ALTERNATIVA) comprises a network of psychologists, social workers and family therapists engaged in research and education on systemic practice and family psychotherapy. In Moldova, the Health for Youth Association (HYA) supports publicly funded youth clinics that deliver preventive and therapeutic services addressing sexual and reproductive health, psychological well-being, substance misuse and violence prevention.

The intervention is scheduled to be delivered to the intervention group between fall 2025 and summer 2026. In Moldova, implementation will occur in a single wave, while in North Macedonia it will be conducted in two waves, based on the feasibility of recruiting families. This approach is consistent with procedures successfully used in North Macedonia during phase 2 of the FLOURISH project.

### Participants and recruitment

The study will include one primary adolescent and one primary caregiver per participating family. Secondary adolescents and secondary caregivers are also eligible to participate in the intervention, although their data will not be included in the primary analyses. Families will be recruited through the implementing organisations, ALTERNATIVA in North Macedonia and HYA in Moldova, as well as their affiliated service delivery networks. Recruitment will follow a structured process, with each group expected to include approximately 10 adolescent–caregiver pairs. Caregivers and adolescents aged 10–14 years will be first invited through multiple channels. After initial interest and verbal consent, country research coordinators will conduct screening interviews to determine eligibility. Table 1 summarises the eligibility and exclusion criteria for participating families.

**Table 1 T1:** Inclusion and exclusion criteria for adolescents and caregivers

Participant	Inclusion criteria	Exclusion criteria
Adolescents	Aged 10–14 years at preassessment. Have lived with the caregiver in the same household for at least four nights per week over the past month. Provided informed assent. Adolescents aged ≥14 must provide informed consent in addition to caregiver consent (per North Macedonian legal/ethical guidelines). Fluent in at least one local language used in the study (Macedonian, Romanian, Russian or Albanian).	Severe psychological problems or acute mental disabilities (these participants will be referred to other mental health services). Participation in a previous phase of the FLOURISH project.
Caregivers	Aged ≥18 years at preassessment. Have lived with the adolescent in the same household for at least four nights per week over the past month. Provided written informed consent for themselves and the adolescent. Fluent in at least one local language used in the study (Macedonian, Romanian, Russian or Albanian).	Severe psychological problems or acute mental disabilities (these participants will be referred to other mental health services). Participation in a previous phase of the FLOURISH project.

FLOURISH, Family-Focused Adolescent & Lifelong Health Promotion; PLH, parenting for lifelong health.

Based on findings from previous phases of the FLOURISH project, recruitment in phase 3 will be expanded to better reach vulnerable families through both education and health system channels. In North Macedonia, this will include training school staff, psychologists, social workers and educational personnel to support recruitment efforts, as well as targeted outreach to families residing in family houses supported by SOS Children’s Village and Albanian-speaking communities. In Moldova, families will be recruited through Youth Klinic (YK) beneficiaries and health-promoting school partners using individual discussions, parent meetings at YKs and schools and informational announcements at YKs. Additional efforts will be made to include Russian-speaking families affected by displacement or regional instability related to the war in Ukraine and residents of the administrative-territorial units on the left bank of the Dniester river, also known as Transnistria.

Intervention staff will include facilitators, supervisors and supporting and coordinating personnel in each country, affiliated with the implementing organisations ALTERNATIVA in North Macedonia and HYA in Moldova. All intervention staff must be at least 18 years old, complete mandatory training, commit to their assigned roles in programme delivery, supervision or assessment, and provide written informed consent. An example of the caregiver informed consent form is provided in online supplemental appendix 2. Facilitators are professionals, some of whom have prior experience in parenting interventions, trained to deliver the PLH programme, lead group sessions and support adolescents and caregivers. Supervisors are senior staff members who oversee facilitators, monitor intervention fidelity and conduct facilitator supervisions and fidelity evaluations. Data assessors are trained research staff responsible for administering standardised assessments and ensuring high-quality, accurate data collection.

### Sample size

We performed a simulation-based power analysis for a baseline-adjusted linear mixed model with random intercepts for families nested in clusters, a fixed effect for treatment (PLH vs waitlist), timepoint (postintervention, follow-up), the treatment-by-time interaction and baseline measures as a covariate, using the R- package simr.^35^ We assumed an effect size of Cohen’s d=0.25 for the treatment effect at post-intervention, a within-person correlation of r=0.6 between baseline, post-intervention and follow-up measures, a between Intracluster Correlation Coefficient of 0.01, an alpha level of 0.05, and no further gains or losses at follow-up compared with post-intervention. Simulation results (1000 iterations) indicated that 62 clusters, each consisting of 10 families, achieve 84% power to detect an effect size of Cohen’s d=0.25 at postintervention and 82% power for the likelihood ratio test, comparing the model that includes the baseline covariate, time, the treatment main effect and the treatment-by-time interaction to the reduced model that contains only the baseline covariate and time. To achieve this sample size requirement in the presence of dropout, we plan to recruit 64 clusters and allow for cluster sizes slightly exceeding 10 families.

While the anticipated individual-level effects may be modest, as this is a preventive intervention, even small effects can translate into meaningful public health benefits when applied across a large number of individuals. Small shifts in risk or symptom trajectories, when sustained and broadly implemented, have the potential to prevent a substantial number of adverse outcomes and reduce downstream clinical burden.

### Randomisation and blinding

This study will involve a multicountry, cluster/group randomised controlled trial of the adapted PLH programme. Clusters will be randomly assigned to either the intervention group or the waitlist control group (see online supplemental appendix 3 figure S1 for the study flow chart). Each group (intervention and waitlist control) will consist of 10 adolescent–caregiver pairs, with a total of 32 groups per country, implemented across 16 sites in North Macedonia and 16 sites in Moldova.

Randomisation will occur at the group level and be based on predefined clusters with two clusters embedded within each geographical region (ie, school or youth clinic A and B). Stratified randomisation with country as the strata will be employed. A total of two sets with 16 sites/clusters will be randomised within each of the countries for a total of 64 sites/clusters overall. In North Macedonia, eligible site/clusters will be primary schools in Macedonian-speaking and Albanian-speaking urban and suburban areas of the Skopje metropolitan region. In Moldova, site/clusters will be Youth Clinics or schools. Across both countries, two clusters (ie, groups) per geographical region will be randomly assigned to either the intervention or the waitlist control condition.

The list of sites/clustered will be provided to the University of Klagenfurt, randomisation will be conducted independently by the University of Klagenfurt and provided to the research coordinators in North Macedonia and Moldova. The random allocation sequence will be generated by the project coordinator at the University of Klagenfurt using a computerised randomisation tool. Participants and data assessors will be blinded during informed consent and baseline assessments. After baseline is completed, participants will be informed of their allocation to intervention group or waitlist. Data assessors will remain blinded during the post and follow-up assessments. Pre, post and follow-up data sent to the analysis team will remain blinded until analyses are completed and shared with the team. To minimise assessment bias, different researchers will be responsible for outcome assessments and process monitoring.

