### Statistical analyses

Prior to effectiveness analyses, descriptive statistics, internal consistencies and correlations will be examined for all study variables. Descriptive statistics will be reported separately for each country and for the total sample. Drop-out analyses will be conducted to compare completers and non-completers of the assessments using analysis of variance and χ² tests. Primary analyses will compare intervention and waitlist control groups at post-intervention and 6-month follow-up using an intention-to-treat approach. No interim analyses are planned. Missing data will be handled via multiple imputation or full information maximum likelihood.

Treatment effects over time will be estimated using baseline-adjusted linear mixed models including fixed effects for treatment group, time and the treatment-by-time interaction, with random intercepts to account for families nested in groups and repeated observations. The treatment effect will be estimated using baseline-adjusted linear mixed models including treatment, time and treatment-by-time interaction terms. To this end, we will use linear mixed models with random intercepts, accounting for clustering at the group or site level, as appropriate, using robust standard errors or multilevel modelling approaches. Effect estimates, CIs and exact p values will be reported for the prespecified outcomes. Analyses will be performed in Mplus, Stata or R, using robust methods or multilevel models.

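### The article does not say whether each region's two clusters are split between the arms, and it uses the word site for 32 units in one sentence and 64 in another

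*Protocol article*

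**What the plan says.** All but two of the relevant statements stand in the protocol article under Randomisation and blinding.

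- **Stratum.** "Stratified randomisation with country as the strata will be employed". No other stratum, block or pairing factor is named.
- **Regional structure.** Randomisation is at group level and uses "predefined clusters with two clusters embedded within each geographical region (ie, school or youth clinic A and B").
- **Assignment within region.** In both countries, "two clusters (ie, groups) per geographical region will be randomly assigned to either the intervention or the waitlist control condition". The text does not say that one of the two goes to each arm.
- **First site count.** There are to be groups of 10 pairs, "with a total of 32 groups per country, implemented across 16 sites in North Macedonia and 16 sites in Moldova".
- **Second site count.** "A total of two sets with 16 sites/clusters will be randomised within each of the countries for a total of 64 sites/clusters overall".
- **What these units are.** For one country the article says that "eligible site/clusters will be primary schools in Macedonian-speaking and Albanian-speaking urban and suburban areas of the Skopje metropolitan region". The Moldovan units are Youth Clinics or schools.

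The Sample size section agrees with the larger count: "we plan to recruit 64 clusters and allow for cluster sizes slightly exceeding 10 families". The Statistical analyses section lists treatment, time, their interaction and the baseline value, with random intercepts for families within groups. It then speaks of "accounting for clustering at the group or site level, as appropriate, using robust standard errors or multilevel modelling approaches".

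**The concern.** A reader cannot tell from this text how the list is to be restricted. Defining an A and a B cluster in each region suggests that the two are meant to be split between the arms, since otherwise the pairing does nothing for the allocation. But the only restriction actually named is country. A statistician handed this section could write either program and claim to have followed it.

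The two uses of the word site add to this. Under one, a site is a place that hosts two groups. Under the other, it is the randomised cluster itself, a single school or clinic. The analysis section then offers group or site as alternative levels of clustering. That choice means nothing if the two words name the same unit, and it matters if they do not.

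At stake are the reproducibility of the allocation, the regional balance that the A/B pairs could deliver, and the match between the analysis and the randomisation.

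**Working it through.** **1. Reproduce the stated number of clusters.**
- 32 groups per country × 2 countries = 64.
- 2 sets × 16 × 2 countries = 64.
- The Sample size section also plans 64, and the 660 adolescents in the Abstract give 660/64 = 10.3 families per cluster, which fits sizes slightly above 10.

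The number of randomised units is therefore not in dispute.

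**2. Count the sites.** The first statement gives 16 + 16 = 32 sites, each with 32/16 = 2 groups. The second gives 64 sites/clusters. The two agree only if site means a region or location in the first sentence and a school or clinic in the second. The article does not say so.

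**3. Compare the allocation rules that the text allows.** Two inputs are inferred, because the article states neither outright: 16 regions per country (32 clusters ÷ 2 per region), and 16 clusters per arm in each country.

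*Country as the only restriction, 16:16.* Fix the arm of cluster A. Of the other 31 clusters in the country, 15 share that arm, so

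P(A and B in the same arm) = 15/31 = 0.484.

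- Expected per country: 16 × 15/31 = 7.7 of 16 regions.
- Expected overall: 32 × 15/31 = 15.5 of 32 regions.
- In 20,000 simulated lists the mean was 15.5, with a 95% range of 10 to 20.

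*Independent coin tosses.* P = 0.5, so 32 × 0.5 = 16 of 32 regions on average.

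*One cluster per arm within each region.* P = 0, so 0 of 32 regions.

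**4. Follow the consequence into the analysis.** Treatment is assigned to the group. If a site is a single school or clinic with one group, clustering by group and by site are the same thing. If a site is a location with two groups, one in each arm, a random intercept for site alone would leave the variation between groups within a site unmodelled, and that is the level at which treatment varies. The article leaves the meaning of site open, so the phrase about group or site level cannot be resolved from the text. The fixed effects listed include neither country nor region, so the strata used for allocation are not in the model as described.

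**The case against.** A fair defence has several parts.

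**The sentences can be reconciled.** Naming country as stratum does not exclude finer blocks, and regional pairs are nested in country. With 16 locations per country, two clusters in each, and one of each pair per arm, every sentence can be satisfied. This stands. A reader might infer that the article describes incompatible designs, but it does not. One-per-arm within region is itself an inference, so it cannot be set against the stratum sentence as a contradiction.

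**Shared premises are not shown.** The sentence with 16 sites per country might suggest that a programme group and a waitlist group meet in the same building, with programme content leaking across. The wording about school or youth clinic A and B, and the description of North Macedonian clusters as primary schools, point to separate premises. The documents give no figure for leakage, so no dilution of the effect can be claimed.

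**Language balance is not promised.** A reader might infer that pairing was meant to balance Macedonian-speaking and Albanian-speaking schools. The article does not say that A and B in a region share a language.

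**A country-only list is valid.** This also stands. The treatment comparison remains unbiased, and the loss is in chance balance and precision. The plan's own ICC suggests a modest loss. With 10 families per cluster and ICC 0.01, the variance factor is 1 + 9 × 0.01 = 1.09, of which 10 × 0.01 = 0.10 comes from differences between clusters. Even if all of that were regional, exact regional balance could remove at most 0.10/1.09 = 9% of the variance, before baseline adjustment.

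**Detail may be held elsewhere.** The flow chart and the statistical analysis plan are not shown, and the model already has families nested in groups. This stands in part: the final covariance structure can be left to the analysis plan. But the article itself states the stratum, the regional pairs and the site counts, so the difficulty lies in what it says and not in what it omits.

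**Conclusion.** The point holds as an ambiguity with a practical consequence. The article names only country as a stratum, builds regional A/B clusters without saying that they are split, and uses site for both 32 and 64 units. The 64 randomised clusters are consistent.

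If the list is restricted by country alone, about 48% of regions (15.5 of 32) would have both clusters in one arm; if regions are blocks, none would. These figures assume 16 regions per country and equal allocation within country. Nothing in the article shows which list was or will be drawn, so the 48% is the consequence of one permitted reading and not an established fact about the trial.

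Neither reading makes the trial invalid. The case for acting is that clarification costs almost nothing, blocking on region would secure balance from pairs already defined, and the analysis can then be matched to the randomisation.

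**What to change.** 1. **Allocation.** State that region, nested in country, is the randomisation block, with exactly one of its two clusters going to each arm. If the list was already drawn with country as the only restriction, report that and remove the wording that implies assignment within region.
2. **Site.** Give the word one meaning, use it throughout, and say whether there are 32 or 64 physical schools or clinics.
3. **Analysis.** In Statistical analyses, replace the choice between group and site level with clustering at the randomised group. Include in the model the strata actually used for allocation: region if it was the block, or country if only country was used.

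**Cost.** A few sentences and a check of the allocation script; the A and B clusters already exist. Modelling region uses degrees of freedom. With 32 regions as fixed effects, the cluster-level count is 64 − 32 − 1 = 31, against 64 − 2 − 1 = 61 with country alone. That is still workable.
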